### Vaccination Process

On the days of each subsequent vaccination, criteria for continued eligibility will again be reviewed and verified. A history-directed physical examination will be done and axillary temperature, blood pressure, pulse and baseline gen-eral symptom history will be recorded. Venous blood will be collected for laboratory analysis as detailed in Section 9.2.1.

After the identity of the subject is checked (by comparing the SID number and photographs in source document with the parent/subject’s photo ID), subjects will be vaccinated by intra-muscular injection into the right or left anterolateral thigh muscles, unless a compelling reason for an alternate injection site is evident (See also SSP No. SM-04: Vaccination Day Procedures). All vaccinations will be done in a fashion that maintains double blinding (See Section 10.5.1). Every effort will be made to vaccinate all 45 children in a given cohort on a given vaccination day.

Although all the foregoing dates are provisional (circumstances may require delays of up to 5 weeks), vaccinations will occur on or about Study Days 0, 14, and 28 (Dose 1); 29, 42, and 56 (Dose 2); and 57, 70, and 84 (Dose 3). The dose-by-dose scheme is as follows:

Dose 1/Study Days 0, 14 & 28: The first 45 subjects to be vaccinated (Dose 1a) will receive either 1/5th dose = 10 ug of FMP-1 (10 subjects in each of 3 age groups = 30) or Imovax® (5 subjects in each of 3 age groups = 15). Grand total = 45.

Two weeks later (Study Day 14), or up to 5 weeks later if temporary discontinuation is deemed necessary, a second 45 subjects will be vaccinated (Dose 1b) with either ½ dose = 25 ug of FMP-1 (10 subjects in each of 3 age groups = 30) or Imovax® (5 subjects in each of 3 age groups = 15). Grand total = 45.

Two weeks later (Study Day 28), or up to 5 weeks later if temporary discontinuation is deemed necessary, a third 45 subjects will be vaccinated (Dose 1c) with either full dose = 50 ug of FMP-1 (10 subjects in each of 3 age groups = 30) or Imovax® (5 subjects in each of 3 age groups = 15). Grand total = 45. At this point (after Dose 1c is administered) all 135 study subjects will have been recruited and vaccinated once.

(2) Dose 2/Study Days 29, 42 & 56: The first 45 subjects to be vaccinated a second time (Dose 2a) will receive either 1/5th dose = 10 ug of FMP-1 (10 subjects in each of 3 age groups = 30) or Imovax® (5 subjects in each of 3 age groups = 15) on Study Day 29. Grand total = 45.

Two weeks later (Study Day 42), or up to 5 weeks later if temporary discontinuation is deemed necessary, a second 45 subjects will be vaccinated (Dose 2b) with either ½ dose = 25 ug of FMP-1 (10 subjects in each of 3 age groups = 30) or Imovax® (5 subjects in each of 3 age groups = 15). Grand total = 45.

Two weeks later (Study Day 56), or up to 5 weeks later if temporary discontinuation is deemed necessary) a third 45 subjects will be vaccinated (Dose 2c) with either full dose = 50 ug of FMP-1 (10 subjects in each of 3 age groups = 30) or Imovax® (5 subjects in each of 3 age groups = 15). Grand total = 45. At this point (after Dose 2c is administered) all 135 study subjects will have been vaccinated twice.

(3) Dose 3/Study Days 57, 70 & 84: The first 45 subjects to be vaccinated a third time (Dose 3a) will receive either 1/5th dose = 10 ug of FMP-1 (10 subjects in each of 3 age groups = 30) or Imovax® (5 subjects in each of 3 age groups = 15) on Study Day 57. Grand total = 45.

Two weeks later (Study Day 70), or up to 5 weeks later if temporary discontinuation is deemed necessary, a second 45 subjects will be vaccinated (Dose 3b) with either ½ dose = 25 ug of FMP-1 (10 subjects in each of 3 age groups = 30) or Imovax® (5 subjects in each of 3 age groups = 15). Grand total = 45.

Two weeks later (Study Day 84), or up to 5 weeks later if temporary discontinuation is deemed necessary) a third 45 subjects will be vaccinated (Dose 3c) with either full dose = 50 ug of FMP-1 (10 subjects in each of 3 age groups = 30) or Imovax® (5 subjects in each of 3 age groups = 15). Grand total = 45. At this point (after Dose 3c is administered) all 135 study subjects will have been vaccinated thrice.

NB: All “a” doses are the 1/5th dose = 10ug dose (Cohort A); all “b” doses are the ½ dose = 25 ug dose (Cohort B); all “c” doses are the full dose = 50 ug dose (Cohort C).

**Table 6: MAL-031 Timelines for Vaccinating each Cohort (Dosage Group)**

|  | Apr 2003 | May | June | July | Aug + 5 mo |
| --- | --- | --- | --- | --- | --- |
| Cohort A | **1a**  Screening | **2a** | **3a** |  | SAE Follow-Up  (Immunogenicity F/U: Aug + 8 mo) |
| Cohort B | **1b** | **2b** | **3b** |
| Cohort C | **1c** | **2c** | **3c** |

### Post-immunization Evaluation Procedures

Immediately after immunization, each subject will proceed to the next station for assessment of local and systemic reactions. Each subject will be observed for 60 minutes post-vaccination or longer if necessary. Signs and symptoms (pain, swelling, fever [defined as axillary temperature  37.5°C], drowsiness, loss of appetite, and irritability/ fussiness) will be solicited from subject and parent and then recorded in the source document by an evaluator according to adverse events recording procedures as outlined in Section 11.

Subjects will complete a one week follow-up after each vaccination (5 visits: day of vaccination, plus days 1, 2, 3 and 7 post-vaccination) at the WRP Kombewa Clinic. All AEs will be followed until resolution (see Section 11). If any solicited signs or symptoms persist beyond the first four days post-vaccination, the subject will be followed daily until resolution of the adverse event. Unsolicited adverse events will be followed as deemed appropriate by the investigator. At each visit, the subjects will be evaluated by soliciting post vaccination signs and symptoms from the parent and by examination of the injection site. A full physical exam will be performed on Day 7 (Visit 5). Scheduled clinic visits will also be conducted on post-vaccination days 14 and 30 (the latter may coincide with the subsequent vaccination day visit). Every effort will be made to insure parental and subject compliance with visits. However, if a parent and subject do not appear for a scheduled clinic visit, a clinician or designee (e.g., field worker) will attempt to contact them on the same day. The staff member who contacts the subject will measure vital signs and collect information on any solicited or unsolicited symptoms for the previous 24 hours. If the clinician determines that the subject has experienced a serious adverse event (SAE), appropriate measures will be taken to notify the Local Medical Monitor (LMM), the DSMB, the IRBs and sponsor (See Section 11.5.2).

### Field Workers: Activities & Competencies

Field workers will undergo a 2-3-week training period during which they will be taught basic study procedures such as taking vital signs, preparing blood smears and additional didactic information regarding malaria and other general health concerns. At the end of this period they will be tested on their knowledge and skills. Only those who satisfactorily pass the test will participate in the study.

Throughout the study period and monthly after the third dose of vaccine, field workers will assist in tracking the location of parents/subjects and in reminding parents of scheduled visits.

Field worker supervisors will visit a sample of subjects periodically to insure that field workers are indeed tracking and collecting the required information (See SOP No. 101.08, v2: Fieldworker Evaluation).

### Long-term Follow-up Period

Study day 120, marks the beginning of a 4-month “Post-vaccination Safety Surveillance Period for SAEs” (Day 120  14 to Day 240  14), which is in turn followed by a 4-month “Long-term Follow-up Period” (Day 240  14 to Day 364  14). Subjects are to be followed for SAEs only through Study day 240 (or Study month 8, i.e., 6 months after last dose). Malaria episodes occurring after this period are not defined as AEs or SAEs and are not reported as such. However, during the “Long-term Follow-up Period”, immune responses and malaria episodes will be documented (See Table 7).

After the end of the “Follow-up Period for Unsolicited AEs” (Day 120), available data will be compiled into an Interim Safety Data Report (statistical analysis) and submitted to the DSMB in early October 2003 (around Day 157). However, the PI and field team members will remain blinded to all results until 30 days after the 30 day post-vaccination follow-up visit for Cohort C’s third vaccine dose; unblinding of “by individual” study results will not occur until the end of the “Post-vaccination Safety Surveillance Period” (Day 240; See Section 13.6 for fuller details).

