# SUMMARY:

| **Title** | A double blind, randomized, controlled, dose escalation phase I field trial in 12 to 47 month old children in western Kenya to evaluate the safety and immunogenicity of WRAIR’s MSP-1 (FMP-1) malaria vaccine adjuvanted in GlaxoSmithKline Biologicals’ AS02A versus rabies vaccine |
| --- | --- |
| **Study Population** | Healthy 12-47 month old, malaria-exposed children |
| **Study Site** | The Walter Reed Project Kombewa Clinic at Kombewa Town, Kombewa Division, Kisumu District, Nyanza Province, wertern Kenya (and two small field stations within Kombewa Division) |
| **Objectives** | ***Primary***   To assess the safety and reactogenicity of the FMP-1/AS02A malaria vaccine in malaria-exposed children living in western Kenya and aged 12-47 months |
|  | ***Secondary***   assess the humoral immune response to the FMP-1/AS02A malaria vaccine in malaria-exposed children living in western Kenya and aged 12-47 months |
| **Study design** | - A phase I, dose escalation (1/5, ½, full dose) vaccine trial in children - Double blind, randomized, controlled (Imovax® Rabies vaccine). - One study center, with 2 outlying field stations |
| **Number of Subjects** | One hundred thirty-five (135) subjects of both genders will be enrolled. Screening/enrollment of subjects will be incremental until the desired number of subjects has been reached. |
| **Number of**  **Cohorts** | Each of 3 study cohorts will consist of 30 children receiving a dose (10, 25, or 50 g; Cohorts A, B, and C, respectively) of the study test article and 15 child-ren receiving the comparator vaccine (45 subjects per cohort). All test article and comparator groups will be further divided into 3 age groups (12-23, 24-35, and 36-47 months) of 10 (test article) or 5 (comparator) subjects each. |
| **Immunization**  **Schedule** | 0, 1, and 2 months (Provisionally: Study Days 0, 29, and 57 for Cohort A; 14, 42, and 70 for Cohort B; 28, 56, and 84 for Cohort C) |
| **Study Duration** | 12 months per subject |
| **Route** | IM injection into (alternately) right & left anterolateral thigh muscles |

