| **Primary endpoint** | The primary endpoints are measures of the safety and reactogenicity of the vaccine as determined by:   Occurrence of solicited symptoms during a 7 day follow-up period after each vaccination (5 visits: day of vaccination and days 1, 2, 3, and 7)   Occurrence of unsolicited symptoms during a 30 day follow-up period after each vaccination (day of vaccination and the 29 subsequent days)   Occurrence of serious adverse events during an 8 month follow-up period  following the first dose of study vaccine |
| **Secondary endpoints** |  Antibody responses to MSP-1 by ELISA following immunization with the study vaccine through 364 days following the first dose of study vaccine |

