# STUDY DESIGN & METHODOLOGY

## Overview

- Double blind, randomized, controlled, dose escalation, phase I study of a candidate vaccine/adjuvant
- One study center, with 2 outlying (satellite) field stations
- Screening will be incremental & will be done within 35 days prior to the first inoculation for each cohort.
- 135 subjects will be divided equally among 3 cohorts (1/5, ½ or full dosage groups: 10, 25 or 50 g, respectively) of 30 subjects each and a comparison group of 15 subjects (Total subjects per cohort = 45).
- Each cohort will be stratified byage group (12-23, 24-35, and 36-47 months) (Total subjects in each of 3 age groups [among all cohorts]= 45).
- The comparison groups (total of 45 subjects in all 3 age groups) will receive Imovax® Rabies vaccine.
- Immunization schedule will be 0, 1, and 2 months for all cohorts (Provisionally: Study days 0, 29 and 57 for Cohort A; 14, 42, 70 for Cohort B; and 28, 56, 84 for Cohort C)
- Vaccinations of Cohorts B and C (FMP-1 doses of 25 ug and 50 ug respectively, with control subjects) will be offset (“staggered”): Cohort B following Cohort A by 2 weeks and Cohort C following Cohort B by 2 weeks. These intervals may be extended for up to 5 weeks, however, if *temporary discontinuation* (see Section 7.9.1) is deemed advisable due to SAEs or other concerns.
- Subjects in each cohort will be randomized separately from the other cohorts, at the times of first vaccinations.
- Route of inoculation will be by IM injection into right or left (alternately) antero-lateral thigh muscles (unless compelling reason for an alternate injection site is evident).
- Study duration will be approximately 12 months per subject.
- Seven (7) day follow-up period for solicited adverse events (5 visits: Vaccination day plus days 1, 2, 3 and 7 post-vaccination)
- Thirty (30) day follow-up period for unsolicited adverse events (Vaccination day plus 29 subsequent days)
- Follow-up of serious adverse events (SAE’s) for 8 months after the first dose of study vaccine (6 months after dose 3)
- At the end of the follow-up period for unsolicited AEs (i.e., after the third dose; Study day 90), subjects will be followed by field workers at home at monthly intervals and will be asked to return to clinic every 3 months for long-term clinical and immunogenicity follow-ups.

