## Adverse Event Follow-up & Assessment of Outcome

Investigators should follow-up subjects with SAEs until the event has subsided, or until the condition has stabilized, regardless of when this occurred in relation to the study conclusion. Investigators should follow-up subjects with non-serious AEs until study conclusion for a given subject. Thus, all follow-ups for a given cohort end on the same calendar day, but the day follow-ups end is different for each cohort. This will be exactly 8 months after the last subject of a given cohort was enrolled into the study. Re-ports relative to the subsequent course of an AE noted for any subject must be submitted to the Study Monitor.

Outcome should be documented as one of the following:

1 = Recovered without sequelae

2 = Recovered with sequelae

3 = Ongoing at subject study conclusion

3a = Ongoing and worsened

3b = Ongoing, but improved

3c = Ongoing and unchanged

4 = Died

5 = Unknown

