## Primary Endpoints

Occurrence of solicited symptoms during a 7 day follow-up period after each vaccination (5 visits: day of vaccination and days 1, 2, 3, and 7)

Occurrence of unsolicited symptoms during a 30-day follow-up period after vaccination (day of vaccination and 29 subsequent days)

Occurrence of any SAEs during an 8 month follow-up period following the first dose of study vaccine (i.e., 6 months following the last dose)

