## Preliminary Analysis

Safety, reactogenicity, and immunogenicity data after 3 vaccine doses will be compiled by Statistics Collaborative, Inc., Washington, D.C. from the CRF data trans-cribed on site in Kenya. This will initially be done after the end of the “Follow-up Period for Unsolicited AEs” (Day 120), when all available data will be complied into an Interim Safety Data Report (statistical analysis) for submission to the DSMB in early October 2003. The Final Safety Data Report to the DSMB will be compiled after the end of the “Post-vaccination Safety Surveillance Period for SAEs” (Day 240) for submission in November 2004. For both reports, safety will be analyzed for dose group overall and by age and dose group without revealing the assignment of individual subjects. The PI and Kenya field team members will remain blinded until one month (30 days) after the 30 day post-vaccination follow-up visit for Cohort C’s third vaccine dose (according to the current provisional daily schedule, that visit comes on Study Day 114 and so unblinding would be on Study Day 144). This unblinding will be a “by group”, but not a “by individ-ual” unblinding. (The purpose of this partial unblinding is to allow assessments of the "by group" data which are requisite for the planning of any subsequent phase I or phase II pediatric trials of MSP-1 -- particularly where dosages and sample sizes are concerned.) The full study unblinding for individual results will be after the end of the “Post-vaccination Safety Surveillance Period for SAEs” (Study Day 240).

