| 119 | 25 AUG |  |  |  |  |
| 120 | 26 AUG |  |  |  | End “Follow-up Period for Unsolicited AEs”; Begin “Post-vaccination safety surveillance period for SAEs” (To Study day 240) |
| 121 | 27 AUG |  |  |  |  |
| 122 | 28 AUG |  |  |  |  |
| 123 | 29 AUG |  |  |  |  |
| 124 | 30 AUG |  |  |  |  |
| 125 | 31 AUG |  |  |  |  |
| 126 | 01 SEP |  |  |  |  |
|  |  |  |  |  |  |
| 144 | 19 SEP |  |  |  | Partial (“by group”) unblinding of study data  (Or 30 days after the 30 day post-vaccination F/U visit for Cohort C’s 3rd dose) |
|  |  |  |  |  |  |
| 156 | 01 OCT |  |  |  |  |
| 157 | 03 OCT |  |  |  | Interim Safety Data Report (from SCI) |
|  |  |  |  |  |  |
| 187 | 01 NOV |  |  |  |  |
|  |  |  |  |  |  |
| 217 | 01 DEC |  |  |  |  |
|  |  |  |  |  |  |
| 239 | 23 DEC |  |  |  | End post-vaccination safety surveillance period for SAEs |
| 240 | 24 DEC |  |  |  | Begin long-term follow-up period for malaria & immunogenicity (Study days 240-364);  Formal full (“by individual”) study unblinding |
| 248 | 01 JAN 04 |  |  |  |  |
|  |  |  |  |  |  |
| 279 | 01 FEB 04 |  |  |  |  |
|  |  |  |  |  |  |
| 307 | 29 FEB |  |  |  | Leap Day! |
| 308 | 01 MAR |  |  |  |  |
|  |  |  |  |  |  |
| 339 | 01 APR 04 |  |  |  |  |
|  |  |  |  |  |  |
| 364 | 26 APR 04 |  |  |  | End long-term follow-up period for malaria & immunogenicity |

| ??? | NOV 04 |  |  |  | Final Safety Data Report |
| --- | --- | --- | --- | --- | --- |

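### Full individual unblinding is fixed at Study Day 240 on the common calendar, before Cohorts B and C can complete the SAE window of the primary endpoint

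*Protocol*

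**What the plan says.** The SAE primary endpoint in Section 13.1 is "Occurrence of any SAEs during an 8 month follow-up period following the first dose of study vaccine (i.e., 6 months following the last dose". A footnote to Table 9 expresses the second part as 180 days after the last injection and labels that point Study day 240.

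Dosing is staggered. Cohort A is provisionally vaccinated on Study Days 0, 29 and 57, and the others on "14, 42, and 70 for Cohort B; 28, 56, and 84 for Cohort C".

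Section 8.1.5 gives one stopping point: "Subjects are to be followed for SAEs only through Study day 240 (or Study month 8, i.e., 6 months after last dose". The calendar in Section 17.2.5 has a single row, "End post-vaccination safety surveillance period for SAEs", at Day 239 (23 December 2003). The next row, Day 240, carries formal full unblinding by individual. Neither row distinguishes cohorts. Sections 10.5.2 and 13.6 also place full unblinding after the end of SAE surveillance and give the day as 240.

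Section 11.4 says follow-up ends on a different day for each cohort and specifies: "This will be exactly 8 months after the last subject of a given cohort was enrolled into the study".

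**The concern.** A single Day 240 cannot be the end of an 8-month window for three cohorts that start two weeks apart. One of two things then happens in Cohorts B and C. Either the SAE window is completed and its last weeks are observed with individual codes open, or the window is cut at Day 239/240 and is shorter than the endpoint requires.

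SAE occurrence is a primary endpoint, and under Section 11.3 the investigators judge whether the vaccine contributed. Open codes could influence both detection and causality rating. The cohort most affected on either reading is the one given the highest dose.

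The disputed days also lie in a transmission season, which Section 4.8 places from November through January. Section 8.1.5 says malaria episodes after the SAE period are not AEs or SAEs, while Section 11.1.1 makes every non-elective hospitalization an SAE. A Cohort C child hospitalized with malaria on Day 250 (3 January 2004) would be a primary-endpoint event under Section 11.4 and no event under the Section 17.2.5 calendar.

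**Working it through.** **Inputs.** First and third doses (Sections 7.1 and 17.2.1): A on Days 0 and 57 (28 April, 24 June 2003); B on Days 14 and 70 (12 May, 7 July); C on Days 28 and 84 (26 May, 21 July). The endpoint window is 8 months from first dose, or 6 months (180 days) from last dose. Under the Glossary a child is enrolled on receiving a first dose, so the Section 11.4 clock starts at dose 1. Section 8.1.2 aims to vaccinate a whole cohort on one day.

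**The plan's own figure.** On the generic schedule in Section 8.2, dose 3 is on Day 60, and 60 + 180 = 240. For Cohort A's calendar, 24 June plus 6 calendar months is 24 December 2003, which is Day 240. So Day 240 reproduces for Cohort A.

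**Which clock the unblinding rule uses.** Sections 10.5.2 and 13.6 number Cohort C's 30-day visit after dose 3 as Study Day 114, and 84 + 30 = 114. On Cohort C's own clock that visit would be about Day 90. The Day 240 given for full unblinding in the same text is therefore on the common calendar, as the date 24 December 2003 in Section 17.2.5 confirms.

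**If the calendar is applied literally (status at Day 240):**

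| Cohort | Days since dose 1 | Days since dose 3 | Short of 180 |
|---|---|---|---|
| A | 240 − 0 = 240 | 240 − 57 = 183 | none |
| B | 240 − 14 = 226 | 240 − 70 = 170 | 10 |
| C | 240 − 28 = 212 | 240 − 84 = 156 | 24 (24/180 = 13%) |

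Using the whole 14-day window around Day 240 (Day 254), Cohort B reaches 184 days but Cohort C reaches 170, still 10 short.

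**If follow-up runs per cohort (day on which the window ends):**

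| Cohort | Dose 3 + 180 days | Dose 1 + 240 days | Dose 3 + 6 calendar months | Dose 1 + 8 calendar months |
|---|---|---|---|---|
| A | 237 | 240 | 240 | 244 |
| B | 250 | 254 | 254 | 259 |
| C | 264 | 268 | 268 | 273 (26 January 2004) |

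Subtracting 240, Cohort B has 10 to 19 days and Cohort C 24 to 33 days of SAE follow-up after individual unblinding. The spread depends on which definition of the window is used.

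**Sensitivity to slippage.** Sections 7.1 and 8.1.2 allow each two-week offset to become up to five weeks. With both at five weeks, Cohort C starts on Day 70 and, keeping the 56 days between its first and third doses, receives dose 3 on Day 126. If Day 240 were left unmoved, Cohort C would have 240 − 126 = 114 days after dose 3, 66 short of 180. A complete window would end on Day 306 (126 + 180) or Day 310 (70 + 240).

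**The case against.** The strongest reply is that the protocol does intend a per-cohort clock, so no child is under-followed. Much of the text supports this. Table 7 says its study days are for Cohort A only. Section 8.2 schedules cohorts independently. The Table 9 footnotes run SAE collection to 180 days after the last injection and treat study-day numbers as nearly common to all cohorts. Section 11.1.3 records SAEs through the sixth month after the last vaccination. Even the Section 8.1.5 sentence glosses Day 240 as 6 months after the last dose. This stands: a reader might infer that the plan deliberately shortens follow-up as dose rises, but that is only one reading. It does not rescue the unblinding date, for which no cohort-specific version appears anywhere.

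A reader might also infer a bias in favour of the 50 µg dose. Each cohort has 15 concurrent rabies recipients with the same follow-up, and Section 13.4 prefers comparing FMP-1 recipients with their own cohort's comparators. Truncation would leave that comparison balanced. Only comparisons across cohorts are exposed, and Section 13.5.3 expects SAEs to be rare.

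The calendar is labelled provisional, and Section 13.6 says unblinding comes after surveillance ends, which would permit a later date. That wording helps, but the printed Day 240 contradicts it for Cohorts B and C even if every dose is given on schedule.

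Three further inferences are not supported:
- **By-group release.** Section 13.6 says "The PI and Kenya field team members will remain blinded until one month (30 days) after the 30 day post-vaccination follow-up visit"; the visit meant is the one following dose 3c. This release at Day 144 is by group, has a stated planning purpose and opens no individual code.
- **Unsolicited AEs.** Section 7.1 has "At the end of the follow-up period for unsolicited AEs (i.e., after the third dose; Study day 90". This fits the generic schedule (60 + 30), and the calendar closes that period on Day 120, after Cohort C's Day 114 visit.
- **Antibody endpoint.** It runs "through 364 days following the first dose of study vaccine", which is already anchored to the dose.

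**Conclusion.** The contradiction is real and limited. Day 240 is right for Cohort A and is printed as the date of full individual unblinding for the whole study. On the per-cohort reading, which the text favours, about 10–19 days of Cohort B's and 24–33 days of Cohort C's SAE follow-up would be observed unblinded. On the literal calendar reading, Cohort C stops at 156 days after dose 3 and 212 after dose 1, so SAE comparisons across dose cohorts rest on unequal follow-up. Comparisons of FMP-1 with rabies vaccine within a cohort are not distorted by unequal follow-up on either reading.

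These figures assume the provisional dosing dates. The larger gap under five-week offsets also assumes that Day 240 is not moved, which the document neither states nor excludes. The effect is modest on the planned calendar, but it concerns a primary endpoint and should be settled before enrolment.

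**What to change.** Reconcile Section 8.1.5, the Day 120–240 entry in Section 8.2, and Sections 10.5.2, 11.4, 13.6 and 17.2.5:
- Define the end of the SAE window from each cohort's, or each child's, own doses, and choose one definition, since 180 days, 6 calendar months and 8 calendar months give different days.
- State that full individual unblinding occurs only after the last Cohort C child has completed that window. On the provisional calendar this is about Day 264–273. If Section 11.4 governs, it is no earlier than Day 273 (26 January 2004). It moves later if doses slip.
- Replace the single Day 239 and Day 240 rows with cohort-specific ends of SAE follow-up and one unblinding row tied to Cohort C.

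The cost is a delay of 24 to 33 days in individual unblinding, up to about five weeks, and, where the calendar would have been applied literally, SAE follow-up of Cohorts B and C extended by the days shown above. No later milestone is affected: long-term follow-up runs to 26 April 2004 and the Final Safety Data Report is due in November 2004.
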